**Objective:**

In this study, we will prospectively compare tunnel anastomosis with the currently more prevalent double-tract jejunal interposition reconstruction technique to further validate its safety and efficacy.

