## Introduction

Gastric cancer is a type of cancer with high morbidity and mortality in China, and the incidence of proximal gastric cancer is currently increasing [1-3]. Surgical treatment for proximal gastric cancer involves either total gastrectomy or proximal gastrectomy. Research has shown that proximal gastrectomy has the same therapeutic potential and efficacy as total gastrectomy, with advantages in terms of postoperative weight loss, dumping syndrome, anemia, and nutritional supplementation [4-10]. However, the issue of reflux esophagitis following proximal gastrectomy remains a significant challenge for surgeons [11]. Numerous studies have been conducted on antireflux techniques for digestive reconstruction, including double-tract jejunal interposition reconstruction and the double-flap technique (Kamikawa anastomosis), which have exhibited promising antireflux effects. Nevertheless, there is still no consensus on which reconstruction method should be considered the standard [12-17].

Tunnel anastomosis is a novel technique for digestive tract reconstruction following proximal gastrectomy. Owing to its preservation of an intact muscular flap, it ensures superior blood supply to the anastomotic site. A previous study by our team demonstrated that the antireflux effects of this technique are favorable [18]. Double-tract jejunal interposition reconstruction is currently the mainstream method for digestive tract reconstruction following proximal gastrectomy and is widely recognized by most experts [19]. The incidence of postoperative reflux esophagitis following this procedure is approximately 10%. Therefore, we selected this technique as the control group to further validate the effectiveness of TA.

We hypothesize that tunnel anastomosis is noninferior to double-tract jejunal interposition reconstruction in preventing postoperative reflux esophagitis. The objective of this study is to further validate the surgical safety and antireflux effect of tunnel anastomosis and assess the efficacy and ability of this technique to improve the quality of life of patients following proximal gastrectomy. It is hoped that this research will contribute to enhancing the theoretical and clinical practice foundations for refining surgical treatment strategies for upper gastric cancer.

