#### Secondary End Points

The secondary study end points include perioperative safety, postoperative nutritional status, and postoperative quality of life.

Perioperative safety primarily encompasses the duration of surgery, amount of intraoperative blood loss, and postoperative complication status. Nutritional status and quality of life following surgery will be assessed at the 3rd, 6th, and 12th postoperative months. Postoperative nutritional status will be determined based on changes in patient weight, hemoglobin levels, total protein levels, albumin levels, total lymphocyte count, and PNI. Additionally, patients’ quality of life will be evaluated via the EORTC QLQ-C30 and daily food intake frequency. The Visick score will be used for assessing patients’ symptoms and quality of life [21]:

Grade I—patients are asymptomatic or have only mild symptoms that do not significantly affect their quality of life. Surgical outcomes are considered excellent.Grade II—patients experience mild symptoms that have minimal impact on their daily activities. Overall, patients are satisfied with the surgical outcome.Grade III—patients have moderate to severe symptoms that affect their daily lives. These symptoms may require medical treatment or lifestyle modifications. The surgical outcome is considered less favorable.Grade IV—patients have severe symptoms that significantly impact their quality of life. The surgical procedure has failed to achieve the desired outcome. Further surgical intervention or other treatments may be necessary.

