### Statistical Analysis

Data analysis will be conducted by professional statisticians. In addition to the overall comparative analysis conducted between the TA and DTJIR groups, we will further perform subgroup analyses stratified by disease stage and surgical approach.

Intention-to-treat and per-protocol approaches will be applied for efficacy analysis. An as-treated approach will be used for safety analysis. For continuous variables, a normality test will be performed first. For those that conform to a normal distribution, the 2-tailed *t* test will be used for statistical analysis (all continuous values will be expressed as means and SDs). Those not conforming to a normal distribution will be presented as quartiles and rank means, and the Mann-Whitney *U* test will be used to calculate the *P* value to compare differences between groups. For categorical variables, the chi-square test will be used for statistical analysis. Repeated-measure data will be analyzed using a mixed-effects model. Subgroup analyses will be conducted by disease stage (early vs advanced); surgical approach (open, laparoscopic, or robot-assisted); age; macroscopic types; and tumor, node, metastasis stage. All *P* values calculated in the analysis will be 2-sided, and *P*<.05 will be considered statistically significant. If missing data constitute more than 5%, multiple imputations will be conducted. Statistical analyses will be performed via SPSS (IBM Corp), Prism (GraphPad Software), or PASS.

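### The article aims to validate surgical safety, but the only inferential rule it states for complications is a two-sided difference test, and a non-significant result from that test cannot support comparable safety

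*Protocol article*

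**What the plan says.** **The aim.** The Introduction states: "The objective of this study is to further validate the surgical safety and antireflux effect of tunnel anastomosis". The Objective paragraph of the Abstract says TA will be compared with DTJIR "to further validate its safety and efficacy".

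**The end point.** Safety is secondary: "The secondary study end points include perioperative safety, postoperative nutritional status, and postoperative quality of life". Its content is given in the same section: "Perioperative safety primarily encompasses the duration of surgery, amount of intraoperative blood loss, and postoperative complication status".

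**The analysis.** Statistical Analysis fixes three things that apply to complications:
- the analysis set: "An as-treated approach will be used for safety analysis";
- the test: "For categorical variables, the chi-square test will be used for statistical analysis";
- the criterion: "All *P* values calculated in the analysis will be 2-sided, and *P*<.05 will be considered statistically significant".

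**What is confined to reflux.** The noninferiority hypothesis (Introduction) and the margin of 0.05 (Power and Sample Size) concern reflux esophagitis only. The article gives no expected complication rate.

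**The concern.** To validate the safety of a new operation against an established one is to make a positive claim: any excess of complications is small enough to accept. A two-sided test of equality is not built for that claim. If it is significant, it shows a difference in one direction or the other. If it is not, the data are compatible with no difference, but they may also be compatible with a sizeable excess. The authors use a noninferiority framework for reflux esophagitis, while the safety half of the same stated objective has only a difference test.

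What is at stake is the safety statement in the final report. By the authors' account in the Discussion, this is the first prospective study of the technique, and they foresee wide use, so that statement will carry weight. If it leaned on a non-significant P value, a real excess could pass as no difference, in a sample sized for another end point.

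**Working it through.** **1. The plan's own figure.** Inputs from Power and Sample Size: reflux esophagitis 10% (DTJIR) and 5% (TA), margin 0.05, one-sided α = .025, power 0.80, dropout 10%.

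n per arm = (1.96 + 0.8416)² × [0.10×0.90 + 0.05×0.95] / (0.05 + 0.05)² = 7.849 × 0.1375 / 0.01 = 107.9, so 108. Then 108 / 0.90 = 120.

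The stated 120 per arm is reproduced. It was derived from reflux esophagitis alone, and complications played no part in it.

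**2. Sample size for the complication comparison.** Data Collection lists postoperative complications among the data gathered before discharge. The 10% dropout allowance therefore matters little here, and 120 per arm is used.

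**3. Chance of missing a true 10-point excess.** The control rate p₁ is an assumption, varied from 5% to 30%. The 10-point excess is also chosen for illustration. With p₂ = p₁ + 0.10 and p̄ the mean of the two:

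Power ≈ Φ{ [0.10 − 1.96 √(2p̄(1−p̄)/120)] / √([p₁(1−p₁) + p₂(1−p₂)]/120) }

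For 10% v 20%: p̄ = 0.15, null SE = √(2×0.15×0.85/120) = 0.0461, alternative SE = √((0.09+0.16)/120) = 0.0456. Power = Φ[(0.10 − 0.0904)/0.0456] = Φ(0.21) = 0.58, so the miss rate is 42%.

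Exact binomial enumeration of the same test gives:

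| Control v TA | Normal approx. | Exact, uncorrected | Exact, continuity-corrected |
|---|---|---|---|
| 5% v 15% | 26% | 24% | 33% |
| 10% v 20% | 42% | 41% | 48% |
| 15% v 25% | 51% | 50% | 57% |
| 20% v 30% | 57% | 57% | 62% |
| 25% v 35% | 61% | 61% | 66% |
| 30% v 40% | 63% | 63% | 68% |

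**4. What one non-significant result can hide.** Suppose 18/120 (15%) v 30/120 (25%) is observed. The pooled rate is 48/240 = 0.20, SE = √(2×0.20×0.80/120) = 0.0516, and z = 0.10/0.0516 = 1.94, P about .053. Under the stated criterion this is not significant. The Newcombe 95% interval for the excess is −0.2 to 20.0 points, so the data do not exclude an excess of nearly 20 points.

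**5. What an interval would deliver.** With similar rates p in both arms, the half-width is 1.96 √(2p(1−p)/120):
- p = 10%: 1.96 × √0.0015 = 0.076;
- p = 25%: 1.96 × √0.003125 = 0.110.

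**6. Scope.** The continuous safety measures are not affected in the same way: at 120 per arm, power for a 0.5-SD difference in duration of surgery or blood loss is about 97%.

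**The case against.** The strongest reply is that the faulty inference appears nowhere in the article. A reader might infer that safety can be concluded only from a non-significant test, or that the authors intend to conclude it that way. The text does not support this. No decision rule for safety is stated, no section says P≥.05 will be read as safe, and the Discussion's preview of the conclusion speaks of effectiveness and the antireflux effect. Nothing prevents a risk difference with an interval from being reported beside the chi-square test. This stands, and the point does not claim otherwise.

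Safety is also a secondary end point, and limited power for a secondary end point is ordinary. A safety margin or interval method may sit in the full protocol or analysis plan, which are not shown, so the absence of a margin is not in itself an error. That stands too.

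The miss rates depend on a control rate and an excess that the documents do not give, so no single figure should be quoted without its condition. Nor do the documents support an argument that patients lost to follow-up would make a favourable safety result easier, because complications are collected before discharge.

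What the reply does not remove is the mismatch in what the article does state: the aim is to validate safety, and the one inferential rule given for complications can detect a difference but cannot establish comparability. Descriptive reporting remains open, but describing is less than validating.

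**Conclusion.** The point holds as a mismatch between the stated safety aim and the stated rule for complications. It does not show that the trial will draw a wrong safety conclusion, it does not rest on a missing margin, and it does not touch the primary reflux analysis.

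For the size: at 120 per arm, with an assumed control complication rate of 5% to 30%, the uncorrected chi-square test misses a true 10-point excess about 24% to 63% of the time. Even at the favourable end of that range, about one such excess in four would go undetected. The rates are somewhat higher if a continuity correction is applied. Different assumed rates or a different excess would change these figures, but not the reasoning that a non-significant difference test is no evidence of comparable safety.

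**What to change.** In Statistical Analysis, for postoperative complications:
- report the risk difference (TA minus DTJIR) with its 95% confidence interval, for example by the Newcombe or Miettinen-Nurminen method;
- base the safety statement on that interval and its upper limit;
- state that P≥.05 will not be read as evidence of comparable safety.

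In the Abstract's Objective and in the Introduction, word the safety aim as estimating safety, unless the investigators prespecify an acceptable upper limit for the excess before the data are analysed. No particular limit is proposed here.

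The cost is a change of wording, with no new data, no more patients and no change to the primary analysis. Recruitment is scheduled to run to February 2027 and follow-up to February 2028, so the change can be made before analysis. The downside is a less favourable claim: given the half-widths above, even equal observed rates of 10% to 25% would leave an excess of up to about 8 to 11 points unexcluded.

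### Every secondary measure may be called significant at two-sided P<.05, with no order, deciding measure or exploratory status; the chance of at least one false secondary finding is about 0.32 (12 tests) to 0.51 (30 tests) at an assumed correlation of 0.5

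*Protocol article*

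**What the plan says.** The Statistical Analysis section of the protocol article gives a single threshold: "All *P* values calculated in the analysis will be 2-sided, and *P*<.05 will be considered statistically significant". It makes no exception for secondary end points.

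The Secondary End Points section names three domains: "The secondary study end points include perioperative safety, postoperative nutritional status, and postoperative quality of life". Each is a bundle of measures:

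- Perioperative safety covers "duration of surgery, amount of intraoperative blood loss, and postoperative complication status".
- Nutrition covers "changes in patient weight, hemoglobin levels, total protein levels, albumin levels, total lymphocyte count, and PNI".
- For the third domain, "quality of life will be evaluated via the EORTC QLQ-C30 and daily food intake frequency", and the Visick score is added for symptoms and quality of life.

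On timing: "Nutritional status and quality of life following surgery will be assessed at the 3rd, 6th, and 12th postoperative months". No measure or visit is named as the one that decides a domain, and the domains are not ordered.

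The Statistical Analysis section also plans a mixed-effects model for repeated measures. It does not say that each visit will be tested separately.

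The Introduction gives the secondary results a role of their own. Besides surgical safety and the antireflux effect, the study is meant to "assess the efficacy and ability of this technique to improve the quality of life of patients following proximal gastrectomy".

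**The concern.** The threshold sentence is a positive rule, not a gap. Followed as written, any one of the secondary comparisons that falls below .05 is declared significant. Nothing makes that declaration depend on the primary noninferiority result, so a secondary benefit could be claimed from a trial that failed its main test.

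This matters here because safety and better quality of life are stated objectives. The Power and Sample Size section also defends the 5% margin by appealing to the new technique's other benefits. It does not list those benefits, but the secondary measures are the natural place to look for them. With several measures per domain and none chosen in advance, which measure (and possibly which visit) to put forward can be decided after the results are seen, in a trial whose Discussion says patients, surgeons and clinical assessors cannot be blinded.

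The point concerns secondary end points in the whole trial population, not the planned subgroup analyses.

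**Working it through.** **1. The plan's own figure.** The only related number in the article is the sample size. Inputs from Power and Sample Size: 10% esophagitis in the control group, 5% with tunnel anastomosis, margin 0.05, one-sided alpha 0.025, power 0.80, dropout 10%.

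n per arm = (1.960 + 0.842)² × (0.10×0.90 + 0.05×0.95) / (0.10 − 0.05 + 0.05)² = 7.85 × 0.1375 / 0.01 ≈ 107.9, so 108. Then 108 / 0.90 = 120.

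This reproduces the stated 120 per arm. One-sided .025 and two-sided .05 agree as levels, so the primary comparison is not in question.

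**2. Counting the secondary tests** (Secondary End Points section).

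- One test per measure, using the planned mixed model for repeated measures: 3 perioperative + 6 nutritional + 3 quality-of-life or symptom = 12.
- Every visit tested as well: 3 + (6 + 3) × 3 = 30.

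The QLQ-C30 is counted once. The 36-Item Short Form Health Survey is left out because it appears under Follow-Up but not among the secondary end points.

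**3. Chance of at least one P<.05 when no secondary difference is real.** For m independent tests it is 1 − 0.95^m. For m tests with common correlation ρ it is

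1 − ∫ φ(t) [Φ((1.96 − √ρ t)/√(1−ρ)) − Φ((−1.96 − √ρ t)/√(1−ρ))]^m dt.

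The article gives no correlations, so ρ is an assumption and a range is shown.

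| Tests | ρ = 0 | ρ = 0.2 | ρ = 0.5 | ρ = 0.8 |
|---|---|---|---|---|
| 12 | 0.460 | 0.428 | 0.319 | 0.186 |
| 30 | 0.785 | 0.722 | 0.507 | 0.256 |

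**4. Only results favouring tunnel anastomosis.** The same model with one tail (z > 1.96, that is 0.025 per test) and ρ = 0.5 gives 0.160 for 12 tests and 0.255 for 30.

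**5. How sensitive the 30-test figure is.** At ρ = 0.5, 30 is the smallest number of tests that passes one half; 27 tests give 0.483. In a simulation of 30 tests with correlation 0.7 between visits of one measure and 0.5 otherwise, the figure is 0.485. With 0.7 and 0.3 it is 0.606. Adding the 36-Item Short Form Health Survey at each visit (33 tests) gives 0.528 at ρ = 0.5.

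**The case against.** The strongest reply is that only a condensed article is at hand, and that multiplicity among secondary end points is usually settled in the statistical analysis plan. That stands as far as a missing hierarchy goes: its absence alone would be no finding. It does not remove the sentence that is present. An analysis plan that treated secondary results as exploratory would have to depart from a rule covering all P values. The label secondary ranks these end points below the primary one but does not limit what may be called significant.

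Three further objections also carry weight:

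- **Number of tests.** A reader might infer that a false secondary claim is more likely than not. The document does not support that. It needs about 30 tests at an assumed correlation of 0.5, and the article plans a mixed model without stating per-visit tests. With 12 tests the figure stays below one half even under independence (0.460).
- **Comparator.** A reader might set these figures against 5% and speak of a multiple of the stated error rate. But 5% is a level per test, and the article never promises a familywise rate for secondary end points.
- **Null and direction.** The figures assume no true secondary difference at all. That is doubtful for operating time, because the two reconstructions differ greatly. The two-sided figures also count false results against tunnel anastomosis; the one-directional figures are about half as large.

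Finally, the Discussion anticipates only that the technique is as effective as the comparator. It makes no secondary superiority claim. That lowers the stakes, but the Introduction's quality-of-life objective remains.

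**Conclusion.** The point holds in a limited form. The article's rule lets each of 12 secondary measures, nine of them assessed at three visits, produce a significance claim without order, deciding measure or exploratory status, and regardless of the primary result.

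On the reading closest to the stated analysis (12 tests), the chance of at least one false significant result is about one in three at correlation 0.5. The 30-test figure of about one half applies only if every visit is tested too. Both rest on the reviewer's assumptions of no true secondary differences and a common correlation, neither of which the article supplies. The inflation is present at every correlation examined, but its exact size is not known.

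This is a cheap improvement to how secondary results will be read. It does not threaten the primary conclusion.

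**What to change.** In the Statistical Analysis section, restrict the significance rule. State that statistical significance will be declared only for the primary noninferiority comparison, and that all secondary end points are exploratory and reported as between-group estimates with 95% confidence intervals.

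If the sponsor wants a formal secondary claim, name one measure and one time point per domain. Test these in a fixed order at two-sided .05, only after noninferiority is shown, and stop at the first non-significant result. All other measures and visits stay exploratory. Whether to take this option is the sponsor's choice.

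The cost is a change of wording, with no new patients or data. Recruitment is scheduled to end in February 2027 and follow-up in February 2028, so it can be made before the final results are known. The small downside is that an isolated secondary P<.05 can no longer be presented as an established benefit.

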## Results

The first patient was enrolled in March 2022, and the recruitment of all 240 patients is expected to be completed by February 2027. Follow-up for these patients is scheduled to conclude in February 2028.

## Discussion

This study may demonstrate that tunnel anastomosis is an alternative method of digestive tract reconstruction following proximal gastrectomy that is as effective as DTJIR. Its antireflux effect may make it one of the most widely used methods of digestive tract reconstruction after proximal gastrectomy.

Proximal gastrectomy is gaining increasing acceptance among the medical community due to its advantages in postoperative nutrition [25]. However, for patients undergoing proximal gastrectomy, postoperative reflux esophagitis is a significant issue. Various anastomotic techniques have been investigated in an attempt to address this problem, yet a standard approach remains elusive [24]. In pursuit of a superior method for digestive tract reconstruction, we modified the Kamikawa anastomosis to develop tunnel anastomosis and conducted a retrospective study. The retrospective study found that tunnel anastomosis is as effective as DTJIR at preventing reflux esophagitis [15,18]. To further validate the preventive effect against reflux esophagitis of this technique, we will conduct this prospective study with the aim of providing a novel reference for digestive tract reconstruction following proximal gastrectomy. Compared with our previous study, this research has a clearly defined objective and rigorous structure. It can also reduce recall bias and control for confounding factors more effectively, yielding more reliable outcomes. Achieving strict adherence to the study protocol will also take longer.

To our knowledge, this is the first prospective study on this technique. To ensure the quality of the enrolled patients, we used stringent inclusion and exclusion criteria in this study. As this is a multicenter study, surgeons are required to possess extensive surgical experience to ensure the quality of the surgical procedures. The operative processes of patients will be documented through video and photographic records. We have also meticulously designed the subsequent follow-up and data analysis protocols. This well-considered design leads us to expect a genuine and reliable conclusion.

This study also has certain inherent limitations. It is not possible to blind patients, surgeons, radiologists, or clinical assessors in this trial. Both the physicians and patients have a clear understanding of the surgical procedure that will be performed. To minimize the bias introduced by the inability to implement blinding, the follow-up and data analysis will be conducted by different people. Meanwhile, as a prospective study, it may have the capacity to mitigate the impact of such bias on the results. The primary end point of this study is the 1-year incidence rate of reflux esophagitis. However, this fails to reflect the long-term antireflux effect. In the future, we will conduct longer-term follow-up to investigate the long-term efficacy of tunnel anastomosis. To increase the dissemination of our research, we will also present our study and its results at a wide range of academic conferences.
